## Abstract

**Introduction:**

Critically ill patients experience high rates of thromboembolic and bleeding events despite the use of pharmacological thromboprophylaxis or weight-based anticoagulation. Laboratory assays for drug monitoring, as Anti-factor Xa (Anti-Xa), overcome the limitations of activated partial thromboplastin time (aPTT) but only quantify drug effects and do not reflect global haemostasis. Viscoelastic testing (VET) may provide additional functional information. Robust clinical data in the ICU setting are limited.

**Objective:**

Primary objective is to assess the association between VET clotting time (CT) in Russell viper venom (RVV) assay and Anti-Xa activity. Secondary objectives include assessing whether VET or Anti-Xa aligns more closely with global haemostatic function, defined by thrombin generation assay (TGA) variables. Exploratory analyses aim to characterise associations among VET parameters, standard laboratory tests, and biomarkers; model dose–exposure–response relationships; and identify clinical modifiers as sepsis or renal dysfunction. Sepsis status will be incorporated as predefined effect modifier in mixed-effects models.

**Study design:**

This single-center, prospective, observational cohort study enrols critically ill adults receiving unfractionated heparin (UFH) or low-molecular-weight heparin (LMWH). Sampling is standardized to pharmacokinetics: 4 h post-dose for subcutaneous LMWH and 4–6 h post-start for i.v. UFH. At each time point, Anti-Xa, VET on ClotPro® (RVV, EX, and RVH assays), standard laboratory tests, and advanced haemostatic markers (factor VIII, factor XIII, PF1 + 2, TGA, PAP, PAI, TFPI, TAT) are collected. Two repeated measurements per patient capture intra-individual variability.

**Expected results:**

We hypothesize that CT-RVV demonstrates a clinically interpretable monotonic relationship with Anti-Xa activity under ICU conditions. We further anticipate discordance between Anti-Xa and global haemostatic markers in a relevant subset of patients, particularly in sepsis, supporting the hypothesis that VET aligns more closely with functional haemostasis than Anti-Xa alone. These findings are expected to delineate when fixed dosing is insufficient, identify predictors of under- or over-anticoagulation, and guide personalised anticoagulation strategies. If RVV-CT consistently correlates with Anti-Xa across clinical states, VET could streamline monitoring where laboratory turnaround time limits timely dose adjustment; if not, the results will clarify the boundaries of VET applicability and highlight scenarios requiring laboratory confirmation or TGA.

**Registration:**

Ethics approval was obtained from the responsible committee of Technical University Dresden (BO-EK-338082024). The study is registered with the German Clinical Trials Register (DRKS00037385), registration date: 10 July 2025, https://drks.de/search/de/trial/DRKS00037385.

## Introduction

1

Thromboembolic events remain a major cause of morbidity and mortality in critically ill patients (1–4). Despite pharmacological prophylaxis, 5–15% of patients in intensive care units (ICUs) develop deep vein thrombosis (DVT), which is associated with prolonged mechanical ventilation and extended ICU and hospital stays (5–8). Low-molecular-weight heparins (LMWHs) are preferred over unfractionated heparin (UFH) because of their greater antithrombotic efficacy and lower complication rates (9, 10). Optimal anticoagulation requires the risk of thrombosis and bleeding to be balanced. Although LMWHs are often assumed to have predictable pharmacokinetics permitting fixed dosing without monitoring, this assumption does not apply in critical illness. The reported therapeutic failure rates range from 12 to 20%, underscoring the potential value of individualized anticoagulation guided by therapeutic drug monitoring (TDM) (2, 4, 11). Prospective studies have demonstrated wide interindividual variability in Anti-Xa activity despite standardized dosing, largely due to sepsis, multiorgan failure, endothelial dysfunction, and fluid shifts (12, 13). A systematic review of 18 studies including 1,644 ICU patients reported low peak Anti-Xa levels ranging from 0.1 to 0.35 IU/mL, although no consistent association with bleeding was revealed (14). These results indicate that fixed dosing may result in both under- and overtreatment (15–17). Anti-Xa monitoring is already recommended for specific comorbidities, such as obesity and renal impairment (1, 10), but its routine use in ICUs is limited by logistical barriers and turnaround times. Moreover, while Anti-Xa accurately reflects drug concentration, it does not capture the global haemostatic status, which may be profoundly altered in critical illness (18). Standard laboratory tests (SLTs), such as aPTT, fibrinogen, and INR, correlate poorly with anticoagulant effects in ICU patients and are influenced by factors unrelated to heparin activity, such as elevated factor VIII, resulting in misleading results (18, 19). Anti-Xa measurement directly quantifies the pharmacodynamic effects of UFH and LMWH and is considered the reference standard (1, 10, 19), but it remains an incomplete surrogate for haemostatic balance. Viscoelastic testing (VET) offers functional, point-of-care (POC) assessment of coagulation, integrating plasmatic and cellular components in real time. Devices such as TEG6s®, ROTEM®, and ClotPro® measure clot initiation, propagation, firmness, and fibrinolysis in whole blood (20, 21). Several studies have attempted to correlate VET variables with Anti-Xa activity, with mixed results. *In vitro* experiments using TEG6s® demonstrated strong correlations between clotting time (CT) and heparin concentration, with classification accuracies >90% for UFH and >78% for LMWH (22). Healthy volunteer studies have shown a strong correlation between TEG® reaction time and Anti-Xa (*r* = 0.82) and improved prediction using composite variables (23). Modified ROTEM® assays demonstrated near-linear relationships between Anti-Xa and CT (*r* ≈ 0.93) in spiking experiments (24). However, the clinical data are inconsistent: some studies reported no correlation between TEG® reaction time and Anti-Xa beyond single peak levels after LMWH dosing (25); others reported that conventional ROTEM® variables failed to detect prophylactic LMWH effects (26), whereas modified ClotPro® assays showed improved sensitivity (27). Overall, the sensitivity of LMWH to VET appears to be highly context- and assay-dependent (28). Thrombin-generation assays (TGAs) provide a complementary global evaluation by quantifying thrombin kinetics and overall generation. Although their use is hampered by limited standardization, automated TGA platforms have demonstrated good correlation with Anti-Xa at therapeutic LMWH doses and may detect reduced thrombin generation in suspected heparin resistance (29). In critically ill children, the endogenous thrombin potential correlated moderately with the TEG® kinetic time and more strongly with Anti-Xa during extracorporeal support (30). These findings emphasize that Anti-Xa, VET, and TGA capture distinct but overlapping aspects of haemostasis: Anti-Xa reflects drug concentration, whereas VET and TGA integrate functional contributions from coagulation factors, fibrinogen, and platelets (31).

In summary, while Anti-Xa measurement is considered the gold standard for monitoring heparins, its predictive value for adequate prophylaxis or therapy in critically ill patients is uncertain. VET and TGA offer broader insights into haemostasis but yield inconsistent results, particularly at low LMWH doses, and remain poorly standardized. Major gaps therefore persist: fixed dosing yields unpredictable Anti-Xa levels; validated therapeutic and prophylactic targets are lacking; the relationship between Anti-Xa and global haemostatic function is unresolved; and the interplay among dosing, Anti-Xa activity, VET, TGA, and patient-specific factors has not been systematically evaluated.

The present protocol addresses these gaps through a prospective observational study in critically ill adults receiving UFH or LMWH. By concurrently measuring Anti-Xa, viscoelastic variables, thrombin generation, and standard laboratory tests, this study aims to determine whether the VET can serve as a reliable surrogate for Anti-Xa monitoring to obtain a broader view of the coagulation system in critically ill patients.

Because Anti-Xa quantifies UFH and LMWH activity in plasma whereas VET reflects whole-blood clot formation influenced by both anticoagulant exposure and the patient’s haemostatic substrate, a strong correlation is not guaranteed in critical illness. The primary objective is therefore pragmatic: to determine whether CT in RVV assay shows a sufficiently stable, monotonic relationship with Anti-Xa to support bedside interpretation as a rapid surrogate for Anti-Xa activity, and to define possible conditions under which this relationship worsens. A stable correlation would support CT-guided interpretation when Anti-Xa results are delayed or logistically constrained; conversely, weak or heterogeneous correlation would question whether VET-based monitoring offers advantages and underscore the need for complementary testing. Associations with clinical outcomes are collected as exploratory signals; the study is not powered to rank assays by clinical endpoints.

## Methods and analysis

2

This trial protocol adheres to the SPIRIT guidance for protocols of clinical trials (32).

### Trial objectives

2.1

*Primary objective:* To assess the association between VET and Anti-Xa in critically ill patients with and without sepsis receiving UFH or LMWH, and to evaluate whether VET can serve as a surrogate for Anti-Xa as the reference assay.

*Secondary objective:* To determine whether VET provides complementary or superior information to Anti-Xa activity for characterizing global haemostatic function, as assessed TGA variables, in critically ill patients with and without sepsis.

*Exploratory objective:* To investigate whether extended VET variables and advanced haemostatic biomarkers provide additional information on anticoagulant effects, to explore dose-exposure-response relationships between drug dose, Anti-Xa, VET, and TGA, to assess the influence of patient-level modifiers, and to generate preliminary signals on the predictive value of laboratory profiles for bleeding and thrombotic complications in critically ill patients with and without sepsis.

Given the observational design and sample size, this study is primarily hypothesis-generating. Clinical events, bleeding and thrombosis, are assessed exploratorily and will be interpreted descriptively without claims of definitive prognostic performance.

### Trial design

2.2

To address the study objectives, this single-center, prospective, observational cohort study will analyse blood samples collected at two time points during the ICU stay of critically ill patients admitted to the Department of Anaesthesiology and Intensive Care Medicine at the University Hospital Dresden, Germany. The first blood sample is obtained at study inclusion. The second sample is collected 24–72 h later. Sampling will be timed to coincide with the expected peak plasma concentration of the administered anticoagulant. Blood sampling for LMWH will be performed 4 h after the last subcutaneous administration to target peak plasma concentration. Sampling will preferentially be obtained from an indwelling arterial catheter using a standardized discard protocol to minimise contamination. For UFH continuous infusion, sampling will occur at steady state (≥4–6 h after initiation or dose adjustment). At each sampling, the following assessments will be performed:

Determination of Anti-Xa activityVET assaysAdvanced coagulation variablesSLTs

The Anti-Xa level at the time of sampling reflects the plasma concentration of the anticoagulant and allows consideration of individual variations in drug absorption and elimination. Interpretation of Anti-Xa activity will account for concomitant antithrombin levels, as assay results depend on endogenous antithrombin when no supplementation is included in the reagent, and may be influenced by reagent composition and acute-phase proteins, particularly in patients receiving UFH. For example, high catecholamine requirements or microcirculatory disturbances, such as those occurring during sepsis, may impair the absorption of subcutaneously administered drugs, leading to subtherapeutic plasma levels and necessitating dose escalation. Conversely, reduced drug elimination, such as in renal failure, may cause accumulation and supratherapeutic levels. To account for the specific haemostatic alterations seen in sepsis, sepsis-specific scores will be recorded. Additional laboratory analyses will include prothrombin fragments 1 + 2 (PF1 + 2), thrombin generation assay (TGA), plasmin-antiplasmin complexes (PAP), plasminogen activator inhibitor (PAI), tissue factor pathway inhibitor (TFPI), and thrombin-antithrombin complexes (TAT) to detect hypercoagulable states and/or impaired fibrinolytic activity. SLTs will also be performed to improve comparability among the heterogenous ICU population and to enable subgroup analyses. The anticoagulants of interest are LMWH and UFH. VET testing will be performed using the RVV-test for LMWH and UFH. Both groups will additionally undergo measurements via extrinsic (EX) and Russell viper venom with heparinase (RVH) tests. Measurements will be performed in patients with prophylactic, intermediate, and therapeutic anticoagulation targets, allowing comparisons of the correlation and adjustability of individualized anticoagulation across different degrees of anticoagulation intensity. Figure 1 provides an overview of the temporal sequence of measurements and planned analyses in the study.

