**Figure 1 fig1:**
[figure not shown]
Study flow and haemostatic assessments in trial. Critically ill patients receiving UFH or LMWH are screened and enrolled consecutively. Two blood samples are obtained per patient: the first at study inclusion and the second 24–72 h later. For LMWH, sampling targets peak plasma concentration at 4 h after subcutaneous administration. For continuous UFH infusion, sampling is performed at steady state, defined as ≥6 h after initiation or ≥4–6 h after dose adjustment. Laboratory analyses include viscoelastic testing (ClotPro® RVV, EX, ECA, RVH ± IN/HI), chromogenic Anti-Xa activity (UFH/LMWH), standard laboratory assays (aPTT, INR, antithrombin, fibrinogen, platelet count, D-dimers), and advanced haemostatic markers (factor VIII, factor XIII, PF1 + 2, TGA, PAP, PAI, TFPI, TAT). All assays are derived from the same sampling time point. Plasma samples for thrombin generation and ELISA-based assays are processed immediately, aliquoted, and stored at −80 °C. These measurements are performed in batch analysis to minimise inter-assay variability. aPTT, activated partial thromboplastin time; ECA, ecarin test; INR, international normalized ratio; LMWH, low-molecular-weight heparin; PAP, plasmin-antiplasmin complexes; PAI, plasminogen activator inhibitor; RVV, Russell’s viper venom test; TGA, thrombin generation assay; TAT, thrombin-antithrombin complexes; TFPI, tissue factor pathway inhibitor; UFH, unfractionated heparin; VET, viscoelastic testing.

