
Specialized haemostasis markers are included to mechanistically characterise discordant profiles between concentration-based heparin activity (Anti-Xa) and functional assays (VET/TGA): PF1 + 2 and TAT as thrombin generation/consumption markers; TFPI as a heparin-responsive anticoagulant pathway marker; PAP and PAI-1 as fibrinolysis activity/inhibition markers. These variables will be analysed descriptively and in focused secondary models to reduce data-driven inference. Table 1 provides an overview about the obtained data.

**Table 1 tab1:** Collected study variables.

Grouping	Variables
Demographic data	Date of ICU admission; Admission diagnosis; Main diagnosis; Gender; Date of birth; Age; Height; Weight; Date of blood collection
Comorbidities	Trauma; Injury Severity Score; Diabetes; Obesity; Coronary heart disease; Chronic arrhythmia; COPD; Other lung diseases; Venous thrombosis; Nicotine abuse; Active tumour disease; Chronic renal insufficiency; Chronic dialysis; Bleeding disorder upon admission; Thromboembolic complication upon admission; Ischemic stroke; Haemorrhagic stroke; Nosocomial infection; Liver diseases
Condition at time of blood collection	Ventilation status; Glasgow Coma Scale; SpO₂; PaO₂; FiO₂; Systolic blood pressure; Diastolic blood pressure; Mean arterial pressure; Heart rate; Catecholamine use and dosage; Inotrope use and dosage; Temperature; Spontaneous respiratory rate; ECMO status; Date of ECMO initiation
Complications within last 24 h	Bleeding (date, volume, transfusion requirements: RBC, FFP, platelets, PPSB, other blood products); Thrombosis; Pulmonary embolism
Severity scores	SOFA; SAPS II
Medication	Sedation and dosage; Platelet aggregation inhibition and dosage; Oral anticoagulation (drug, dosage, time of last intake); Other anticoagulants and dosage; UFH dosage; LMWH dosage and drug name; Parenteral nutrition; Immunosuppressants
Viscoelastic testing (ClotPro®)	LMWH: EX, RVV, ECA, RVH; UFH: EX, RVV, ECA, RVH, IN, HI; Recorded variables: CT, CFT, A5, A10, MCF, Lysis time, Alpha angle
Standard laboratory tests (SLT)	Haemoglobin; Hematocrit; Platelet count; Leukocytes; Prothrombin time (Quick); aPTT; Anti-Xa; dTT; Antithrombin; D-dimer; Fibrinogen; Calcium; Factor VIII; Factor XIII; C-reactive protein; Procalcitonin; Creatinine; Glomerular filtration rate; Urea; ALAT; ASAT; Bilirubin; Albumin; Triglycerides
Advanced haemostatic assays	TAT; PF1 + 2; TGA; PAP; PAI; TFPI

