### Additional analyses

2.16

Dose–exposure–response relationships between administered anticoagulant dose, Anti-Xa activity, and VET parameters will be explored using linear mixed-effects models. Potential effect modification by patient-specific variables (e.g., age, sex, renal function, SOFA score, SAPS II) will be examined using interaction terms within the mixed-effects framework. No separate subgroup analyses are planned. Stratified analyses, if presented, will be considered descriptive. Exploratory analyses of clinical events (bleeding or thrombotic complications) will use logistic regression only if event numbers permit stable estimation. These analyses are considered hypothesis-generating.

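### The exploratory LMWH dose–exposure, target-attainment and renal analyses pool first-dose with repeated-dose samples, so their results depend partly on how early a patient was enrolled

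*Protocol article*

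**What the plan says.** All references are to the protocol article.

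- **LMWH sampling.** Section 2.2: "Blood sampling for LMWH will be performed 4 h after the last subcutaneous administration to target peak plasma concentration". The Figure 1 legend repeats the rule: "For LMWH, sampling targets peak plasma concentration at 4 h after subcutaneous administration". Neither sets a condition on earlier doses.
- **UFH sampling.** Section 2.2: "For UFH continuous infusion, sampling will occur at steady state (≥4–6 h after initiation or dose adjustment".
- **Timing.** Section 2.2: "The first blood sample is obtained at study inclusion", and "The second sample is collected 24–72 h later".
- **Eligibility.** Section 2.3 admits patients on UFH or LMWH whatever the dose, enrolled consecutively, with no minimum prior exposure.
- **Interest in elimination.** Section 2.2 says the level allows individual absorption and elimination to be considered, and gives as an example that "reduced drug elimination, such as in renal failure, may cause accumulation and supratherapeutic levels".
- **Analysis.** In Section 2.10, exploratory outcome 3 relates dose to Anti-Xa, VET and TGA and asks whether dosing reaches the intended Anti-Xa range. It uses every scheduled sampling, stratified by regimen type. Section 2.16 fits linear mixed models and adds: "Potential effect modification by patient-specific variables (e.g., age, sex, renal function, SOFA score, SAPS II) will be examined using interaction terms".
- **Data listed.** Table 1 gives "UFH dosage; LMWH dosage and drug name". For oral anticoagulants it also lists the time of last intake.

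**The concern.** A sample 1 taken at inclusion may follow one patient's first LMWH dose and another patient's tenth. Both count as 4 h peaks at the same dose, and stratifying by regimen type does not separate them. Carry-over from earlier doses is zero in the first and present in the second, and it is largest where elimination is slow.

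Three exploratory results are exposed:

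- the dose–exposure slope, which averages over different exposure histories;
- the statement on target attainment, which mixes first-dose with repeated-dose levels;
- the renal interaction in the dose–exposure model, which is diluted because first-dose samples lack the carry-over that impaired elimination would produce.

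A random intercept for patient does not remove this. Dose number differs between patients at sample 1 and rises within patients from sample 1 to sample 2. The Discussion notes that acute illness may complicate the timing of consent. If sicker patients were therefore enrolled after more doses, dose number would also be associated with the modifiers under study. That is plausible, but the article does not show it.

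**Working it through.** The plan gives no figure on this point, so there is none to reproduce. The check has a count and an illustration of size.

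**1. How many samples can be affected.** Section 2.12 plans 30 LMWH patients with two samples each: 30 × 2 = 60 samples. Only a patient's first sample can normally follow a first dose, because sample 2 comes 24–72 h later. The upper bound is 30 of 60. The article gives no basis for estimating the actual share.

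**2. Carry-over at steady state.** The article gives no half-life or dosing interval, so these are assumptions: half-life 4–7 h with normal and 12–16 h with impaired elimination; dosing interval τ of 12 or 24 h. In a one-compartment model the ratio of the steady-state to the first-dose level is

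R = 1 / (1 − 2^(−τ/t½)).

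| t½ | R, τ = 24 h | R, τ = 12 h |
|---|---|---|
| 4 h | 1.02 | 1.14 |
| 7 h | 1.10 | 1.44 |
| 12 h | 1.33 | 2.00 |
| 16 h | 1.55 | 2.47 |

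Example: t½ = 16 h, τ = 12 h gives 2^(−0.75) = 0.595 and R = 1/0.405 = 2.47.

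**3. Dilution.** If a share f of the pooled LMWH samples is first-dose and the rest are treated as steady state, the average carry-over increment is (1 − f)(R − 1). At the upper bound f = 30/60 = 0.5 it is halved. For t½ = 16 h and daily dosing it falls from 0.55 to 0.275; for t½ = 4 h it falls from 0.02 to 0.01. The loss is therefore concentrated in patients with slow elimination.

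**4. Check with an absorption phase.** With first-order absorption (ka 0.3 and 1.0 per h, assumed) the level at time t after one dose is proportional to

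c(t) = ka/(ka − k) × (e^(−kt) − e^(−ka·t)), with k = ln 2 / t½.

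The 4 h level after n doses is the sum of c(4 + iτ) for i = 0 to n − 1. Steady-state to first-dose ratios, over the two ka values:

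| t½ | τ = 24 h | τ = 12 h |
|---|---|---|
| 4 h | 1.02–1.04 | 1.15–1.32 |
| 10 h | 1.24–1.39 | 1.79–2.26 |
| 20 h | 1.79–2.18 | 2.98–3.95 |

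The direction agrees with step 2.

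**5. What limits the effect.** The same model gives two counterweights.

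- *Sample 2.* For t½ = 20 h and daily dosing, the ratio to the first dose is 1.44–1.67 after 24 h and 1.72–2.08 after 72 h, against 1.79–2.18 at steady state. The recovered share of the increment is 0.44/0.79 = 56% to 0.67/1.18 = 57% at 24 h, and 0.72/0.79 = 91% to 1.08/1.18 = 92% at 72 h.
- *First dose itself.* Half-lives of 7–20 h raise the first-dose 4 h level 1.18–1.52 times relative to a 4 h half-life. Some elimination effect is therefore visible after a single dose.

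**The case against.** The strongest reply is that only exploratory work is touched. Section 2.10 classes dose–exposure and patient-level modifiers as exploratory, and Section 2.1 calls the study primarily hypothesis-generating. This stands, and it limits the point.

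Several stronger readings are tempting, and the article does not support them.

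- *That the primary result is compromised.* The primary analysis (Section 2.13.1) pairs CT-RVV and Anti-Xa from the same sample, so dose number does not bias it. The renal modifier in Section 2.13.2 concerns that same paired relation and is largely untouched.
- *That a renal effect cannot be seen.* Carry-over is absent from first-dose samples, but a first-dose level still carries some elimination signal, and sample 2 recovers much of the rest.
- *That under-anticoagulation is overstated in all patients.* With daily dosing and normal elimination the assumed ratio is 1.02–1.10. The roughly two-fold ratios need 12-hourly dosing with impaired elimination.
- *That different rules for UFH and LMWH are a contradiction.* A plateau for an infusion and a peak for intermittent dosing are each reasonable. What matters is that only one rule conditions on exposure history.
- *That dose time will not be recorded.* Table 1 is an overview, a 4 h rule presupposes a known dose time, and the case report form or analysis plan may hold more. The article also names accumulation only as an example and sets no accumulation parameter as an outcome.

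The stated pooling rule remains after these concessions: all samplings enter, separated by regimen type, and regimen type does not distinguish a first dose from a later one.

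**Conclusion.** The point holds for the exploratory LMWH dose–exposure slope, the target-attainment statement under outcome 3, and the renal interaction within those dose–exposure models. These are diluted, and they depend partly on the number of doses a patient had received before enrolment.

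The size ranges from negligible (normal elimination, daily dosing) to an absent carry-over of 33–55% of the first-dose level (impaired, daily) or 100–147% (impaired, 12-hourly) in each first-dose sample. At most half of the LMWH samples are involved. These percentages rest on assumed half-lives and intervals, and the number of first-dose samples is unknown. It is an inexpensive improvement to exploratory analyses and does not threaten the main result.

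**What to change.** 1. At each LMWH sample, extract from the medication record the dose time, the sampling time and the number of consecutive doses on the unchanged regimen.
2. Include dose number (or first-dose versus repeated-dose) and actual hours since dose as covariates in the Section 2.16 dose–exposure models.
3. Report target attainment under outcome 3 separately for first-dose and repeated-dose samples.
4. Repeat the renal interaction in repeated-dose samples only, as a sensitivity analysis.

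Restricting the main renal analysis to samples after at least three doses is not advised. The cut is arbitrary and costs samples. With t½ = 16 h and 12-hourly dosing, three doses give 1 + 0.595 + 0.354 = 1.95, or 1.95/2.47 = 79% of steady state, so it would also serve least well the patients of most interest.

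The cost is two or three extracted fields, one or two extra model terms in a group of 30 patients, and a smaller set for the sensitivity analysis. Sampling and patient care do not change.

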### Study population and recruitment

2.3

Participant selection is based on predefined inclusion criteria and is conducted entirely on a voluntary basis, with informed consent obtained before participation. Given the biological and clinical heterogeneity inherent to critically ill ICU patients, sufficient sample size is required to allow modelling of patient-level variability and pre-specified effect modification.

Inclusion criteria for critically ill patients are as follows:

≥18 yearsUndergoing anticoagulation therapy with UFH, LMWH at any dosageWritten informed consent by patient or legal representative

The following variables are recorded to enable further classification:

Sepsis or septic shock within the last 48 h according to the SEPSIS-3 criteria (33) using the SOFA score, continuously collected hemodynamic variables and results of blood gas analysis

Exclusion criteria:

Known hereditary coagulation disorderPatients receiving ongoing therapeutic oral anticoagulants (direct oral anticoagulants or vitamin K antagonists) will be excluded from the primary analysis. Patients with prior exposure may be included only if clinically relevant residual drug activity can be excluded based on documented timing and renal function.

All ICU patients treated with UFH or LMWH will be screened, and eligible patients will be consecutively enrolled until the target sample size is reached. Enrolment will be based on fulfilment of the inclusion criteria and will proceed only after fully voluntary informed consent has been obtained. Sepsis status will be defined according to Sepsis-3 criteria (33). SOFA score will be recorded as a continuous variable and additionally explored as a predefined severity modifier (e.g., SOFA ≥ 9) within effect-modification analyses.

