Thus, two correlated measurements correspond to approximately 1.54 independent observations. This results in approximately 13 LMWH-treated and 15 UFH-treated patients required to achieve the planned statistical power per anticoagulant category.

$$\mathrm{LMWH}:\frac{19}{1.54}\approx 13\;\text{patients}$$

$$\mathrm{UFH}:\frac{23}{1.54}\approx 15\;\text{patients}$$

Allowing for a 15% dropout rate and to ensure stable estimation within pre-specified mixed-effects models under heterogeneous ICU conditions, the target sample size was set to 30 LMWH-treated and 36 UFH-treated patients (total *n* = 66).

Sepsis status and other clinically relevant variables will be analysed as pre-specified effect modifiers within the mixed-effects framework rather than as separately powered subgroups.

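### Samples taken soon after a switch between LMWH and UFH can contain both heparins, yet they enter the drug-specific analyses as single-drug samples

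*Protocol article*

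**What the plan says.** Eligibility (section 2.3) requires treatment with UFH or LMWH at any dose and sets no condition on earlier use of the other heparin. The exclusion criteria deal with ongoing oral anticoagulants and then add: "Patients with prior exposure may be included only if clinically relevant residual drug activity can be excluded based on documented timing and renal function". In its place, directly after the oral agents, that sentence reads as applying to them only.

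Sampling is timed by the current drug. For UFH, section 2.2 has: "For UFH continuous infusion, sampling will occur at steady state (≥4–6 h after initiation or dose adjustment". The legend of Figure 1 differs on the time after initiation: "sampling is performed at steady state, defined as ≥6 h after initiation or ≥4–6 h after dose adjustment". For LMWH: "Blood sampling for LMWH will be performed 4 h after the last subcutaneous administration to target peak plasma concentration". On the repeat sample: "The second sample is collected 24–72 h later". No rule covers a change of heparin before inclusion or between the two samples.

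Table 1 lists the medication data as: "Oral anticoagulation (drug, dosage, time of last intake); Other anticoagulants and dosage; UFH dosage; LMWH dosage and drug name". A time of last intake appears for oral agents only.

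Drug type has two levels throughout. It is a fixed effect in the primary model and the stratifier for the Spearman coefficients (2.13.1), and a predefined effect modifier (2.12). Recruitment is counted the same way: "the target sample size was set to 30 LMWH-treated and 36 UFH-treated patients". There is no mixed or switched category.

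**The concern.** Section 2.2 treats Anti-Xa as a readout of the concentration of one administered anticoagulant. The Discussion describes the assay as heparin-dependent inhibition of a fixed amount of added factor Xa. On that description both heparins contribute to one reading, and the assay cannot separate them.

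A patient moved from LMWH to an infusion therefore qualifies as a UFH sample within hours, while LMWH from the last injection may still be active. The protocol itself names the setting in which this lasts longest: "Conversely, reduced drug elimination, such as in renal failure, may cause accumulation and supratherapeutic levels".

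Three sets of results are exposed: the correlations reported by drug, the drug-type interaction, and the dose–exposure–response models, where part of the Anti-Xa value would have no link to the recorded current dose. The label also decides which tests are run, because IN/HI (2.7) and factor VIII (2.6) are for UFH patients only.

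**Working it through.** The plan states no figure on this point, so there is none to reproduce. The check has three parts.

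**1. Can a mixed sample pass the stated rules?** Take a patient whose last LMWH dose was g hours before the UFH infusion began and who is sampled s hours after that start.
- Eligibility is met, because the patient is on UFH.
- The residual-drug criterion does not apply, because no oral agent is involved.
- The UFH timing rule is met at s = 4–6 h (section 2.2) or s = 6 h (Figure 1).
- The sample is labelled UFH. That the label follows the current drug is inferred; the article gives no other basis.

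So such a sample is admitted under either timing statement.

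The reverse switch is probably less troublesome. If UFH reaches steady state within 4–6 h, as the protocol says, first-order kinetics imply that it also clears on about that scale. Little should then remain 4 h after an LMWH dose, provided the infusion stopped by the time of that dose.

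**2. How much LMWH could remain?** Inputs:
- LMWH peak at 4 h (section 2.2).
- First-order decay after the peak (assumed).
- Half-life of 4–12 h, the upper end standing for reduced clearance (assumed; not in the documents).
- g = 12 h (assumed), with g = 24 h for comparison.

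Share of peak remaining = 0.5^((g + s − 4)/half-life).

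| Half-life | g = 12, s = 4 | g = 12, s = 6 | g = 24, s = 4 | g = 24, s = 6 |
|---|---|---|---|---|
| 4 h | 12% | 9% | 2% | 1% |
| 6 h | 25% | 20% | 6% | 5% |
| 8 h | 35% | 30% | 12% | 11% |
| 12 h | 50% | 45% | 25% | 22% |

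In IU/mL for g = 12 h:
- At the ICU peak range of 0.1–0.35 IU/mL cited in the Introduction: 0.09 × 0.1 ≈ 0.01 to 0.50 × 0.35 ≈ 0.18.
- At an assumed peak of 1.0: 0.09 to 0.50.

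The slope is reported per 0.1 IU/mL, so these are about 0.1–1.8 and 0.9–5 reporting units.

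**3. Does residual LMWH bias the UFH estimates?** CT and Anti-Xa come from the same blood, so both may respond. A simple simulation used 36 UFH-labelled patients with one sample each. Every input was assumed: mean UFH activity 0.4 IU/mL, mean residual LMWH 0.3 IU/mL in switched patients, pure-UFH correlation about 0.6, and 20% of patients switched (about 7 of 36).

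| CT response to LMWH relative to UFH | Slope relative to pure UFH | Mean Spearman (about 0.55 if none switched) |
|---|---|---|
| 0.25 | 0.76 | 0.51 |
| 0.5 | 0.83 | 0.55 |
| 1.0 | 1.00 | 0.62 |

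The slope falls or does not change. The rank correlation can fall, stay level or rise. The assumed 0.3 IU/mL lies above the 0.18 obtained at the cited ICU peaks, so this is towards the unfavourable end.

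**The case against.** The strongest reply is that this is a condensed article. Section 2.13 refers to a statistical analysis plan to be finalised before database lock, and rules for labelling samples often sit there. That is fair for the labelling rule. It does not cover what the article itself fixes: the sampling times, a residual-drug criterion placed with oral agents only, and a data list with no time for the previous heparin.

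Four stronger readings are tempting, and the documents do not support them.
- *A patient who switches between samples fits neither group.* The 30 and 36 are recruitment targets. Nothing says that drug type is constant within a patient, and a mixed model accepts a value that changes by sample. Per-sample labelling is compatible with the text; it is just not stated.
- *Mixed samples pull the UFH and LMWH relations together.* The simulation shows that this depends on the relative CT response, which is not given.
- *The contamination is 1 to 5 reporting units.* That needs a peak near 1.0 IU/mL. Therapeutic dosing is included, so higher peaks are possible, but the only peak range in the article gives at most about 1.8.
- *The primary analysis is compromised.* As listed, the model has one common slope and no drug-by-Anti-Xa interaction. A wrong label mainly affects the drug offset.

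Two further points stand. The exposed analyses are described as exploratory or descriptive, and the frequency of switching is unknown. Recorded doses might also identify some switched patients, but not how recently the other heparin was given.

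**Conclusion.** The gap is real. The stated rules admit recently switched samples into the drug-specific analyses under a single-drug label, and the listed data would not reliably identify them afterwards. The effect on the primary common slope is probably small. In the stratified correlations, the drug-type interaction and the dose–exposure models, neither size nor direction can be determined from the documents. The 9–50% of peak and the slope ratios of 0.76–1.00 are illustrations under the assumptions listed, not estimates for this study. The point merits correction because UFH and LMWH results are to be reported separately from small groups, and dose times not recorded at sampling may be hard to recover later. It does not threaten the study as a whole.

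**What to change.** 1. State that anticoagulant type is assigned per sample.
2. Add to the case report form the date and time of the last dose of each heparin, including the one stopped.
3. Extend the protocol's existing residual-activity criterion, based on documented timing and renal function, to the other heparin, and use it to flag samples as mixed. Fix the look-back before database lock and make it longer where renal function is reduced. A flat 24 h would not be enough under the assumptions above: 0.5^((24 − 4)/8) leaves 18% of the LMWH peak, and 0.5^((24 − 4)/12) leaves 31%.
4. Leave mixed samples out of the drug-specific estimates, the drug-type interaction and the dose–exposure models. Keep them in the overall analysis, with a sensitivity analysis without them, and report their number.
5. Reconcile section 2.2 and Figure 1 on the minimum time after the start of UFH.

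The cost is a few lines of protocol text, one or two time fields and a few samples lost from the drug-specific analyses. If switching is rare, almost nothing is lost. Items 1 to 4 are labelling, recording and analysis rules only and do not affect treatment.
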